### **3.4.2.2. Effectiveness/Clinical Response Parameters**

#### **Parameter of Interest**

The parameter of interest to evaluate diagnostic performance of KK1.0 and KK2.0 will be egg counts and intensity of egg load of low, moderate, or heavy per diagnostic method and per STH species as defined in the Data Analyses in Section 4.3 below.

### **3.4.3. Safety Measures**

There will be no safety measures in this study as no Janssen marketed medicinal product is under study in this non-interventional study.

## **4. STATISTICAL ANALYSIS METHODS**

Statistical analyses will be performed by or under the authority of the sponsor. A general description of the planned statistical methods to be used to analyze the data collected in this study is presented in the following subsections.

### **4.1. Determination of Sample Size**

The study is designed to generate descriptive data for informative purpose. No formal hypotheses will be tested. The planned sample size of 500 children is based on pragmatic considerations.

The sample size will be based on enrolling SAC in the in selected STH endemic areas of Ucayali, a remote Amazonian region of Peru. The sample size is considered adequate to evaluate an improved diagnostic method (KK2.0) over the standard of testing for monitoring STH prevalence in LATAM.

### **4.2. Measure to Minimize Bias**

To reduce potential bias during data collection and evaluation, at the 24-hour timepoint slides will be randomly selected for the manual counting (KK1.0 method) first or the KK2.0 slide scanning method second, or vice versa. Randomization will be conducted via sealed envelopes containing a code assigned to the method, ie, KK1.0 or KK2.0, that the lab technician will use first when reading Slide B. Each day the technicians will have 12 Slide Bs to read. They will select an envelope and follow the order of which method to use first and second when reading Slide B.

### 4.3. Data Analyses

#### 4.3.1. Data Analyses

Descriptive summaries will be provided by diagnostic method and STH species. All continuous variables will be summarized using descriptive statistics, which will include the number of children, mean, standard deviation, median, minimum, and maximum. A 95% confidence interval (CI) will also be provided for EPG and sensitivity. All categorical variables will be summarized using frequencies and percentages. Summary and analysis will be provided by diagnostic method, STH species, and timepoints (30 minutes and 24 hours). It should be noted that at the 24±4-hour timepoint the same slide (Slide B), will be evaluated by both the KK1.0 and KK2.0 methods. While at the 30-minute timepoint, different slides (slides A and B) from the same stool sample will be evaluated by the same 2 methods. Therefore, extra caution should be exercised when comparing results from the different methods at the 30-minute timepoint since 2 different slides are being analyzed.

Egg load will be classified into 3 intensity categories as detailed below according to EPG:

- *A. lumbricoides*: Low: <5,000 EPG; Moderate: 5,000-49,999 EPG; Heavy: >50,000 EPG
- *T. trichiura*: Low: <1,000 EPG; Moderate: 1,000-9,999 EPG; Heavy: >10,000 EPG
- Hookworms: Low: <2,000 EPG; Moderate: 2,000-3,999 EPG; Heavy: >4,000 EPG

Since TSET method cannot produce EPG, intensity of each STH species will only be derived for KK1.0 and KK2.0 methods.

Since no “gold” standard for egg counts exist in this study, a diagnostic pseudo “gold” standard will be created. A sample is considered to be truly positive if any diagnostic method comes back with a positive reading at any time of the study.

Number of total positive samples for a STH species is defined as

$$N(+) = N(KK1.0(+))_{30m} \cup KK2.0(+))_{30m} \cup KK1.0(+))_{24h} \cup KK2.0(+))_{24h} \cup TSET(+))$$

Where  $KK1.0(+))_{30m}$  indicates a positive sample based on KK1.0 at 30 minutes,  $KK2.0(+))_{30m}$  indicates a positive sample based on KK2.0 at 30 minutes,  $KK1.0(+))_{24h}$  indicates a positive sample based on KK1.0 at 24 hours,  $KK2.0(+))_{24h}$  indicates a positive sample based on KK2.0 at 24 hours, and  $TSET(+))$  indicates a positive sample based on TSET which is performed only once during the study.

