Janssen GPH Research and Development (R&D) has been evaluating an artificial intelligence digital pathology (AI-DP) based on the KK thick-smear, to achieve WHO goal for the Diagnostic Target Profile of the STH as part of J&J contribution to 2030 NTD goals. The prototype unit has travelled for demonstration and field testing to Tanzania, Cambodia, Kenya, Ethiopia, Washington DC (COR-NTD Innovation Lab) and Belgium. During the course of evaluation, 7,780 field of view images (of approximately 800  $\mu\text{m}$  x 600  $\mu\text{m}$ ) were manually reviewed to verify image quality, image focus, locations and classes of STH eggs. A total of 16,990 parasite eggs have been marked-up and form the ground truth data for training artificial intelligence (AI) models. An open- source relational database built in MySQL (a database management system) manages the data and allows the custom AI-DP development pipeline.

The performance of the technology is summarized as follows:

- *Ascaris lumbricoides*: Sensitivity 96%, Specificity 98%, Precision 98%, Accuracy 97%
- *Trichuris trichiura*: Sensitivity 97%, Specificity 98%; Precision 93%, Accuracy 98%
- Hookworms (*Necator americanus* and *Ancylostoma duodenale*): Sensitivity 96%, Specificity 99%; Precision 97%, Accuracy 99% [1]

Since the frequency (ie, annually or bi-annually) of drug administration in PC programs are based on prevalence and intensity of infections, the AI-DP tool is a more sensitive diagnostic method and that can lead to more successful implementation of STH programs. The WHO has defined threshold criteria to describe low, moderate and heavy infection intensity and is presented below in [Table 1](#) [2].

**Table 1: Fecal Egg Count Thresholds Defining Low, Moderate and Heavy Infection Intensity [2]. The Fecal Egg Counts are Expressed as Eggs per Gram of Stool.**

|                             | Low     | Moderate     | Heavy   |
|-----------------------------|---------|--------------|---------|
| Ascaris lumbricoides | 1–4,999 | 5,000–49,999 | >50,000 |
| Trichuris trichiura  | 1–999   | 1,000–9,999  | >10,000 |
| Hookworms                   | 1–1,999 | 2,000–3,999  | >4,000  |

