#### Analysis of Primary Endpoints

Summary of EPG will be provided by diagnostic method, STH species, and timepoint. A permutation test (5,000 iterations) will be employed for comparison of EPG between different diagnosis methods (KK1.0 and KK2.). The 95% CI will be determined based on bootstrap analysis (5,000 iterations). To preserve the correlation of egg count readings by different diagnostic methods from either different samples or same smear of the same participant, permutations will be done within each participant, not across all participants (ie, in a permutation, once an egg count

reading is randomly assigned to one of the 2 diagnostic methods, the other reading from the same participant will be automatically assigned to the other diagnostic method). Re-sampling in bootstrap will be performed at participant level, and the egg count reading will remain with the same diagnostic method as performed.

Sensitivity for KK1.0 at 30 minutes will be calculated as

$$= \frac{N(KK(1.0(+))_{30m})}{N(+)}$$

Where  $N(KK1.0(+))_{30m}$  is the number of positive samples based on KK1.0 method at 30 minutes. Sensitivity for other diagnostic methods and other timepoints will be calculated similarly.

A permutation test (5,000 iterations) will be employed for comparison of sensitivity between different diagnosis methods and the 95% CI will be determined based on bootstrap analysis (5,000 iterations) in similar approach as for EPG. Sensitivity will be calculated for each of the 5,000 iterations, and p-value and 95% CI will be constructed.

Summary of percentages of SAC with low, moderate, or heavy infection intensity will be provided.

2x2 (eggs, no eggs) and 3x3 (low, moderate, or heavy infection intensity) tables based on egg load will be provided to evaluate agreement between different test methods. Weighted Kappa statistics will be provided.

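### The analysis rule for Low intensity has no lower limit and so takes in egg-negative readings, whereas the protocol's own Table 1 starts Low at 1 EPG

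*Protocol*

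**What the plan says.** Section 4.3.1 states the rule: "Egg load will be classified into 3 intensity categories as detailed below according to EPG". The roundworm limits are set as "Low: <5,000 EPG; Moderate: 5,000-49,999 EPG; Heavy: >50,000 EPG". The other two species follow the same pattern: Low is anything under 1,000 EPG for *T. trichiura* and anything under 2,000 EPG for hookworms, again with no lower limit.

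The synopsis (Statistical Analysis of Data) repeats the same limits.

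Table 1 in Section 1.1, which the protocol presents as the WHO criteria, gives the *A. lumbricoides* row as "1–4,999 | 5,000–49,999 | >50,000". Its Low ranges for *T. trichiura* and hookworms are 1–999 and 1–1,999. Zero is outside Low in all three rows.

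The classes feed two of the primary endpoints listed in Section 2. For the first, Section 4.3.1 says "Summary of percentages of SAC with low, moderate, or heavy infection intensity will be provided". For agreement, it plans "2x2 (eggs, no eggs) and 3x3 (low, moderate, or heavy infection intensity) tables based on egg load", with weighted kappa. Neither sentence restricts the analysis to egg-positive readings. Under the secondary endpoints, by contrast, a child counts as infected only if an egg count is positive.

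**The concern.** A reading of 0 EPG is below 5,000, 1,000 and 2,000, and the rule has no other class to hold it. A program that follows Section 4.3.1 to the letter would therefore label every egg-negative child a low-intensity infection. The same child would be uninfected in the prevalence analysis and infected at low intensity in a primary analysis.

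In the 3x3 table, a child with 0 EPG by KK1.0 and, say, 4,896 EPG by KK2.0 (204 eggs × 24) would fall in the Low/Low cell and count as full agreement. The protocol's rationale names weak sensitivity at low intensity as a limitation of KK1.0. The boundary between no eggs and few eggs is thus where the two methods may well differ, and the 3x3 would not show it.

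**Working it through.** The plan has no figure to reproduce: the sample size of 500 is pragmatic and no prevalence is assumed. The check compares the two definitions and then shows what the difference does.

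**1. Which values change class.** The Sample Processing Form (Attachment 1) converts counts to EPG with factor 24, 12 or 8 by stool type, so attainable values are count × 8, 12 or 24 and the smallest non-zero value is 8. I assume the same factors apply to KK2.0. Listing every attainable value for each species and factor, the Section 4.3.1 Low set and the Table 1 Low set differ by exactly one value: 0 EPG. The discrepancy therefore consists of the egg-negative readings and nothing else.

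**2. Effect on the Low percentage.** Let N = 500, p = proportion positive by a method for a species, and m = proportion of positives that are moderate or heavy. Both p and m are assumptions.

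- As written: Low = (N − N·p·m)/N = 1 − p·m
- Under Table 1, as a share of all children: Low = p·(1 − m)

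With p = 0.30 and m = 0.10 there are 350 negatives, 150 positives and 15 moderate or heavy. As written, Low = (500 − 15)/500 = 97.0%. Under Table 1, Low = 135/500 = 27.0%. The difference is the 350 negatives, or 70%.

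| p | m | Low as written | Low under Table 1 |
|---|---|---|---|
| 5% | 5% | 99.8% | 4.8% |
| 5% | 20% | 99.0% | 4.0% |
| 30% | 10% | 97.0% | 27.0% |
| 70% | 5% | 96.5% | 66.5% |
| 70% | 20% | 86.0% | 56.0% |

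Over p from 5% to 70% and m from 5% to 20%, Low runs from 86.0% to 99.8% as written and from 4.0% to 66.5% under Table 1. In every row the gap is 1 − p, the egg-negative share.

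**3. Effect on the agreement table.** Take two invented tables for 500 children, with classes zero, low, moderate and heavy (one method in rows, the other in columns):

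- A: (350, 20, 0, 0), (20, 80, 5, 0), (0, 5, 14, 1), (0, 0, 1, 4). Forty children are positive by one method only; each method is positive in 130/500 = 26%.
- B: the same, except that the first row is (310, 40, 0, 0) and the second is (40, 80, 5, 0). Eighty children are positive by one method only; each method is positive in 150/500 = 30%.

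With zeros placed in Low, the Low/Low cell is 350 + 20 + 20 + 80 = 470 in A and 310 + 40 + 40 + 80 = 470 in B, so the two 3x3 tables are identical. Raw agreement is (470 + 14 + 4)/500 = 97.6%. For linear-weighted kappa, observed weighted disagreement is (5 + 5 + 1 + 1) × 0.5/500 = 0.0120. The expected value, from margins 475, 20 and 5, is 2 × (475×20×0.5 + 475×5×1 + 20×5×0.5)/500² = 0.0574. Kappa = 1 − 0.0120/0.0574 = 0.791.

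| | A (40 discordant) | B (80 discordant) |
|---|---|---|
| 3x3, zeros in Low: agreement; kappa | 97.6%; 0.791 | 97.6%; 0.791 |
| 4x4 with a zero class: agreement; kappa | 89.6%; 0.792 | 81.6%; 0.656 |
| 2x2, eggs or no eggs: kappa | 0.792 | 0.619 |

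Doubling the positive/negative disagreement leaves the 3x3 unchanged. The 4x4 and the 2x2 both register it.

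**The case against.** The strongest reply is that the authors meant egg-positive readings only. The classes are called infection intensity, Table 1 begins at 1 EPG, presence of eggs has its own 2x2 table, and infection is defined elsewhere by a positive count. On that reading zeros never enter Low. This is a plausible account of the intention, and because of it one cannot say that the reported results will be wrong, only that the rule as written gives a wrong result if followed. It does not remove the contradiction, because the analysis section states explicit cut-offs and says nothing of a restriction. Dropping the zeros would also leave open the denominator of the percentages and the place in the 3x3 of a child positive by one method only.

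A reader might go further in three ways that the protocol does not support:

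- *That the agreement endpoint cannot detect disagreement about egg presence.* It can: the planned 2x2 table is there for that. The blind spot is confined to the 3x3, which still separates low from moderate and moderate from heavy.
- *That the Low class would consist mostly of uninfected children.* That depends on prevalence. At 70% positive with 20% of positives moderate or heavy, Low as written holds 150 negatives and 280 positives.
- *That the open upper limit is a second error of the same kind.* Heavy is written as above 50,000, 10,000 and 4,000, which leaves those exact values unclassified. But Table 1 has the same limits, so nothing is contradicted, and the values can occur only with factor 8 (6,250, 1,250 and 500 eggs).

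It is also fair to say that the study is descriptive, that raw counts and a negative field are recorded so the classes can be re-derived at any time, and that denominators and table layout are often left to an SAP. Those points lower the stakes. They do not cover a stated rule that conflicts with the protocol's own table.

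**Conclusion.** The point holds as an internal contradiction. The Low class in Section 4.3.1 and the synopsis lacks the lower limit that Table 1 gives, and the only readings affected are those at 0 EPG. Followed literally, the rule adds every egg-negative child to Low in a primary endpoint and hides negative-versus-low disagreement in the 3x3 table and its weighted kappa. Sensitivity, EPG summaries, the 2x2 table, prevalence, and moderate and heavy counts are unaffected.

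The mechanism is certain; the size is not. The 97% against 27%, and the ranges of 86.0–99.8% against 4.0–66.5%, rest on assumed prevalence and intensity. The kappa values come from invented tables and show only that the 3x3 does not respond to this kind of disagreement. They do not forecast the study's results.

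**What to change.** In Section 4.3.1 and the synopsis:

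1. Set Low to 1–4,999 EPG (*A. lumbricoides*), 1–999 EPG (*T. trichiura*) and 1–1,999 EPG (hookworms), as in Table 1.
2. State the denominator of the intensity percentages: all children with a reading by that method, or egg-positive children only.
3. State how zeros enter the agreement analysis. Either add a Negative (0 EPG) class and compute weighted kappa on a 4x4 table, or keep the 3x3, restrict it to readings positive by both methods, and leave negative/positive discordance to the 2x2. Either is sound; the choice should be written down before the data are analysed.
4. Optionally, close the exact-limit gap for Heavy in the same edit, in Table 1 as well so that the two stay consistent.

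The cost is a change of wording in the protocol, carried into any SAP, and at most one extra row and column per agreement table. No new data are needed.

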## 2. OBJECTIVES AND HYPOTHESIS

### Research Question

The intent of the study is to evaluate the sensitivity of KK2.0 at detecting STH eggs among SAC living in selected STH endemic areas of Ucayali, a remote Amazonian region of Peru.

Since a “gold” standard diagnostic test is not available for detection of intestinal parasites, the operational characteristic (sensitivity) will be estimated using the combined results from KK1.0 and KK2.0 at 30-minute and 24-hour timepoints and TSET (within first hour) (see Objectives below and [Figure 1](#) for schematic flow chart) as a diagnostic pseudo “gold” standard in this study [12].

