| To assess the diagnostic performance of KK2.0 in comparison to KK1.0 at detecting hookworms ( Necator americanus and Ancylostoma duodenale ) and Ascaris lumbricoides and Trichuris trichiura in SAC living in selected areas of Ucayali, a remote Amazonian region of Peru, at the 30-minute and 24-hour timepoints, respectively, of slide preparation. | 
 
Eggs per gram (EPG)
 
Sensitivity of KK1.0 and KK2.0 at 30-minute and 24-hour timepoints
 
Agreement in KK1.0 and KK2.0 results at 30-minute and 24-hour timepoints
 
Percentages of SAC with low, moderate, or heavy intensity of infection by EPG
 
 |
| Secondary                                                                                                                                                                                                                                                                                                                                                                      |                                                                                                                                                                                                                                                                                                                            |
| To evaluate the prevalence STH (hookworms [ Necator americanus and Ancylostoma duodenale ], and Ascaris lumbricoides and Trichuris trichiura ) in the selected endemic, remote Amazonian region of Ucayali, Peru.                                                                                                                                         | 
 
STH prevalence as a percentage in SAC living in the selected areas of Ucayali, Peru
 
                                                                                                                                                                                      |

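### Sensitivity is scored against a reference that contains the reads being compared, so the KK2.0-versus-KK1.0 test credits a false positive exactly like a true extra detection

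*Protocol*

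**What the plan says.** The protocol states that no gold standard exists and creates a pseudo gold standard in section 4.3.1: "A sample is considered to be truly positive if any diagnostic method comes back with a positive reading at any time of the study". N(+) for a species is the union of five reads: KK1.0 and KK2.0 at 30 minutes, KK1.0 and KK2.0 at 24 hours, and TSET.

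Under Analysis of Primary Endpoints, the sensitivity of KK1.0 at 30 minutes has N(+) as denominator and a numerator that "is the number of positive samples based on KK1.0 method at 30 minutes". Then: "Sensitivity for other diagnostic methods and other timepoints will be calculated similarly".

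The primary endpoints include "Sensitivity of KK1.0 and KK2.0 at 30-minute and 24-hour timepoints" and agreement between the two methods; specificity is not among them. The comparison is tested: "A permutation test (5,000 iterations) will be employed for comparison of sensitivity between different diagnosis methods". A p-value and a bootstrap 95% confidence interval go with it, and readings are permuted within participant.

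The same section plans 2x2 (eggs, no eggs) agreement tables with kappa, and the secondary analysis plans prevalence by method. Section 3.4.2.1 describes KK2.0 as AI plus verification by an expert parasitologist. Section 3.1.1 has 100% of KK2.0 recounted, against 10% of KK1.0 and TSET.

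**The concern.** The two methods being compared help to define the truth against which they are scored. Every positive from either method is true by definition, so against this reference every method has 100% specificity and the plan cannot estimate a false-positive rate from it.

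The primary question is whether KK2.0 detects infection better than KK1.0. If KK2.0 calls more samples positive, the planned analysis reports higher KK2.0 sensitivity, with a p-value, whether the extra calls are eggs that KK1.0 missed or objects mistaken for eggs. Those two explanations have opposite implications for adopting the tool.

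**Working it through.** **Inputs.** From the protocol: the union definition of N(+), the sensitivity formula, within-participant permutation, and 500 children ("The planned sample size of 500 children is based on pragmatic considerations"). Not in the protocol, so assumed: true prevalence per species, true sensitivity, and the sample-level false-positive rate of KK2.0 after verification. There is no stated power or precision figure to reproduce.

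**Step 1: what the difference measures.** At one timepoint let b be the number of samples KK2.0-positive and KK1.0-negative, and c the reverse. Both methods share the denominator, so

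difference = [N(KK2.0+) − N(KK1.0+)] / N(+) = (b − c) / N(+).

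**Step 2: one false positive.** Start at 85/100 for both methods. Add one KK2.0 false positive in a sample negative on every other read: KK2.0 = 86/101 = 85.1%, KK1.0 = 85/101 = 84.2%. An infected sample that only this KK2.0 read detects gives the same figures.

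**Step 3: the permutation test.** Swapping the two readings within a child at one timepoint leaves that child's union status unchanged, so N(+) is constant over permutations and the p-value depends only on b and c. With c = 0, b = 5 gives a two-sided p of 2 × (1/2)^5 = 0.0625 and b = 6 gives 2 × (1/2)^6 = 0.031. Nothing in the test depends on whether the b samples are infected.

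**Step 4: illustrative size.** Assume true sensitivity of 80% for both methods, no false positives from KK1.0 or TSET, all truly positive samples found by at least one read, and the same KK2.0 false positives at both timepoints. With prevalence p and false-positive rate f:

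T = 500p; F = 500(1 − p)f; N(+) = T + F; KK2.0 = (0.8T + F)/N(+); KK1.0 = 0.8T/N(+); gap = F/N(+).

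| f | p | T | F | N(+) | KK2.0 | KK1.0 | gap (points) |
|---|---|---|---|---|---|---|---|
| 0.5% | 5% | 25 | 2.375 | 27.375 | 81.7% | 73.1% | 8.7 |
| 0.5% | 10% | 50 | 2.25 | 52.25 | 80.9% | 76.6% | 4.3 |
| 0.5% | 20% | 100 | 2 | 102 | 80.4% | 78.4% | 2.0 |
| 1% | 5% | 25 | 4.75 | 29.75 | 83.2% | 67.2% | 16.0 |
| 1% | 10% | 50 | 4.5 | 54.5 | 81.7% | 73.4% | 8.3 |
| 1% | 20% | 100 | 4 | 104 | 80.8% | 76.9% | 3.8 |

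The true gap is zero in every row. The distortion is largest where infection is rare.

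**Step 5: false positives that do not repeat.** If they fall independently at 30 minutes and 24 hours, then at f = 1% and p = 10% the union is 50 + 450 × (1 − 0.99²) = 58.955. KK2.0 is 44.5/58.955 = 75.5%, KK1.0 is 40/58.955 = 67.8%, and the gap is 4.5/58.955 = 7.6 points. KK2.0 now falls below its true 80%, but the gap still favours it.

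**Step 6: effect on the p-value.** In a simulation of the five-read union (800 runs per setting, 500 children, equal true sensitivity of 80%, exact paired sign test standing in for the permutation test), p < 0.05 occurred in about 19%, 12% and 5% of runs at 5, 10 and 20% prevalence with f = 1%. With f = 0 it occurred in about 1%, 4% and 4%.

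**Step 7: what the other planned outputs reveal.** The 2x2 tables give b and c, and prevalence by method gives the positive totals. At 24 hours both methods read Slide B, so b there is free of between-slide variation; at 30 minutes they read different slides, which adds discordance. None of these outputs says how many of the b samples are infected.

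**The case against.** The protocol is open about the limitation: it calls the reference a pseudo gold standard, cites a source for it, labels the work descriptive and exploratory, and presents its methods as a general description. KK2.0 is not the bare AI, because an expert validates the images and all KK2.0 results are recounted. Both safeguards should lower the false-positive rate. False positives by KK1.0 would offset the effect. All of this stands, and it limits the likely size. It does not change the definition, and the exploratory label sits beside a planned p-value and interval for this very comparison.

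Four stronger readings are tempting, and the documents do not support them.

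- *Nothing planned would reveal the problem.* The 2x2 tables and prevalence by method do show the discordance; what they cannot do is explain it.
- *A KK2.0 false positive always raises KK2.0's sensitivity.* It raises only the affected read. If not repeated, it lowers KK2.0 at the other timepoint.
- *The protocol's own figures imply a 2% false-positive rate.* Section 1.1 reports, for *T. trichiura*, "Sensitivity 97%, Specificity 98%; Precision 93%, Accuracy 98" per cent. Putting 2% into Step 4 at 10% prevalence gives 49/59 = 83.1% versus 40/59 = 67.8%, a 15-point gap. But those figures describe AI models trained on marked-up images. They are not shown to be per sample or after expert verification, so they cannot anchor that number.
- *Slide B supplies three of the five reads, so the reference is tilted to KK2.0.* One of the three is the KK1.0 read at 24 hours, so the tilt is towards the slide and not towards KK2.0 in that comparison.

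It is also true that a method calling everything positive scores 100% sensitivity against any reference. An external reference therefore does not measure specificity; it only keeps false positives in reference-negative samples out of the difference.

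**Conclusion.** The concern holds in this form: the tested contrast is a difference in positive calls divided by N(+), and it cannot tell lost specificity from better detection. That part is algebra from the protocol's definitions and needs no assumption about the tool.

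The size is not known. Under the assumptions in Step 4 the spurious gap is about 2 to 9 points at a residual rate of 0.5%, and about 4 to 16 points at 1%, across 5 to 20% prevalence. These are illustrations and not predictions: the protocol states neither prevalence nor a post-verification rate, and a residual rate near zero would make the gap negligible. No conclusion that KK2.0 does have false positives, or that its result will be inflated, follows from the documents.

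**What to change.** In section 4.3.1 and the matching synopsis text:

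1. Rename the union-based measure relative sensitivity, defined as positivity relative to any-method positive. State that its p-value is not to be read as a difference in true sensitivity.
2. Add a paired KK2.0-versus-KK1.0 comparison among TSET-positive samples, by species and timepoint, with its interval. This reference is common to both methods and contains neither of them.
3. Report the KK2.0-positive/KK1.0-negative and KK2.0-negative/KK1.0-positive counts at each timepoint split by TSET result, including positives found by one method only. Label them descriptive and not an estimate of specificity, since a single-method positive may be a false positive or a true detection that the others missed.

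The cost is wording and a few tables from data already collected. The TSET-positive subset is smaller, so intervals will be wider. TSET is itself imperfect and may over-represent higher egg loads, which weakens the comparison in light infections, where section 1.3 says KK1.0 is least sensitive. The new results should therefore stand beside the union result and not replace it.
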